### 16.3.2 Statistical analysis methods

#### 16.3.2.1 The balance analysis of basic values (comparison between groups of baseline indicators)

- 1) The measurement data will be using t test or Wilcoxon rank sum test;
- 2) Enumeration data between groups will be compared with chi-square test, Fisher's exact probability method or Wilcoxon rank sum test, when appropriate.

#### 16.3.2.2 Efficacy analysis

- 1) Primary outcome:

Survival curves will be estimated for the primary outcome using the Kaplan-Meier procedure and compared using a Cox regression model Wald test, stratified by the opposite arm of the factorial design. First, marginal effects will be compared between intensive and standard antiplatelet therapy, and also between immediate intensive statin therapy (atorvastatin 80mg/d) and delayed intensive statin therapy (atorvastatin 40mg/d). As these are independent comparisons, they have no effect on the type I error rate. For both treatment comparisons, the primary outcome of stroke will be judged to be statistically significant if the treatment test p-value is  $< 0.05$ . Second, if either intensive antiplatelet or immediate intensive statin treatment (atorvastatin 80mg/d) is statistically significant, the effects between combined intensive antiplatelet and immediate intensive statin treatment (atorvastatin 80mg/d) and combined standard antiplatelet and delayed intensive statin treatment (atorvastatin 40mg/d) will be tested. Cox regression model stratified by the opposite arm of the factorial design, will be used in the curative effect assessment and evaluation between the subgroups.

- 2) Secondary outcomes:

- d. Kaplan-Meier curve will be used to simulate the cumulative risk of 90-day follow-up combined with secondary endpoint events such as vascular events, ischemic stroke, TIA, myocardial infarction, vascular death and all-cause death. Cox proportional risk model will be used to calculate HR and the 95% confidence interval and the Log-rank test would be used to evaluate the efficacy;
- e. For ordinal stroke or TIA, ordinal logistic regression will be used to calculate OR and 95% confidence interval. For the poor functional outcome (mRS score 2-6) and early neurological deficits (increase in NIHSS score at 7days) indexes, logistic regression will be used to calculate OR and 95% confidence interval.
- f. The validity of the extreme value would be examined, and the sensitivity analysis would be carried out.

- 3) Safety analysis

The overall of safety assessment is all used test medications and the safety follow-up case should be

recorded at least once. The safety evaluation data includes adverse reactions observed during the trial and changes in laboratory data before and after treatment.

Safety evaluation will be analyzed using safety data set.

Moderate to severe bleeding, intracranial hemorrhage, and overall mortality will be calculated using the Kaplan-Meier curve to simulate the 3-month cumulative risk, and the Cox proportional hazards model to calculate the HR and 95% confidence interval.

For other adverse events and laboratory abnormalities, the cases which was normal before the treatment and abnormal after the treatment would be mainly analyzed and listed, in order to the comparison of differences before and after treatment.

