|                       | 
statin treatment (atorvastatin 80mg/d) and combined standard antiplatelet and delayed intensive statin treatment (atorvastatin 40mg/d) will be tested.
 
2) Secondary outcomes:
 
a. Kaplan-Meier curve will be used to simulate the cumulative risk of 90-day follow-up combined with secondary endpoint events such as vascular events, ischemic stroke, TIA, myocardial infarction, vascular death and all-cause death. Cox proportional risk model will be used to calculate HR and the 95% confidence interval and the Log-rank test would be used to evaluate the efficacy;
 
b. For ordinal stroke or TIA, ordinal logistic regression will be used to calculate OR and 95% confidence interval. For the poor functional outcome (mRS score 2-6) and early neurological deficits (increase in NIHSS score at 7days) indexes, logistic regression will be used to calculate OR and 95% confidence interval.
 
c. Extreme values will be checked for validity and sensitivity analyses will be performed. A two-sided test will be used for all statistics, and <math>P < 0.05</math> is considered statistically significant.
 
3.3 Safety analysis
 
Safety evaluation will be analyzed using safety data set. Moderate to severe bleeding, intracranial hemorrhage, and overall mortality will be calculated using the Kaplan-Meier curve to simulate the 3-month cumulative risk, and the Cox proportional hazards model to calculate the HR and 95% confidence interval. For other adverse events and laboratory abnormalities, the cases which was normal before the treatment and abnormal after the treatment would be mainly analyzed and listed, in addition to the comparison of differences before and after treatment.
 |

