## 2.3 Safety purposes

**2.3.1** To evaluate safety of intensive antiplatelet therapy versus standard antiplatelet therapy for 90 days in acute mild ischemic stroke or high-risk TIA patients attributed to intracranial or extracranial atherosclerosis on the incidence of:

- Moderate to severe bleeding (Appendix 6)
- Intracranial hemorrhage
- Hepatotoxicity: Alanine aminotransferase (ALT) or Aspartate aminotransferase (AST) > 3 times the upper limit of normal value.

- Muscle toxicity: Creatine kinase (CK) > 10 times the upper limit of normal value, or the presence of muscle pain, myopathy, or rhabdomyolysis.
- Death
- Other adverse events (AEs) / severe adverse events (SAEs)

**2.3.2** To evaluate safety of immediate intensive statin therapy (atorvastatin 80mg/d) versus delayed intensive statin therapy (atorvastatin 40mg/d) for 90 days in acute mild ischemic stroke or high-risk TIA patients attributed to intracranial or extracranial atherosclerosis on the incidence of:

- Moderate to severe bleeding (Appendix 6)
- Intracranial hemorrhage
- Hepatotoxicity: Alanine aminotransferase (ALT) or Aspartate aminotransferase (AST) > 3 times the upper limit of normal value.
- Muscle toxicity: Creatine kinase (CK) > 10 times the upper limit of normal value, or the presence of muscle pain, myopathy, or rhabdomyolysis.
- Death
- Other AEs / SAEs

**2.3.3** To evaluate the safety of intensive antiplatelet therapy combined with immediate intensive statin therapy (atorvastatin 80mg/d) versus standard antiplatelet therapy combined with delayed intensive statin therapy (atorvastatin 40mg/d) for 90 days in acute mild ischemic stroke or high-risk TIA patients attributed to intracranial or extracranial atherosclerosis on the incidence of:

- Moderate to severe bleeding (Appendix 6)
- Intracranial hemorrhage
- Hepatotoxicity: ALT or AST > 3 times the upper limit of normal value.
- Muscle toxicity: CK > 10 times the upper limit of normal value, or the presence of muscle pain, myopathy, or rhabdomyolysis.
- Death
- Other adverse events / severe adverse events

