### 4.4 Secondary safety outcomes

- Intracranial hemorrhage
- Hepatotoxicity: ALT or AST  $> 3$  times the upper limit of normal value;
- Muscle toxicity: CK  $> 10$  times the upper limit of normal value, or the presence of muscle pain, myopathy, or rhabdomyolysis.
- Death
- Other AEs / SAEs

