### 5.2 Exclusion criteria

1. Presumed cardioembolic stroke or TIA (e.g. atrial fibrillation, heart valve prosthesis, atrial myxoma, endocarditis, etc.).
2. Other determined etiology of stroke or TIA (e.g. aortic dissection, cervico-cerebral artery dissection, vasculitis, vascular malformation, moyamoya disease/syndrome, fibromuscular dysplasia, etc.).
3. Non-vascular neurological diseases (e.g. intracranial tumor, multiple sclerosis, etc.).
4. Index infarction affects  $\geq 50\%$  of a cerebral lobe (e.g. parietal, frontal, occipital).
5. Hemorrhagic transformation after onset.
6. Contraindications to clopidogrel, aspirin or atorvastatin:
  - a. History of hypersensitivity;
  - b. Severe heart failure (NYHA classification: III- IV) or asthma;
  - c. Coagulation disorder or systemic bleeding;
  - d. History of drug-induced hematologic or hepatic abnormalities;
  - e. Leukopenia ( $< 2 \times 10^9/L$ ) or thrombocytopenia ( $< 100 \times 10^9/L$ );
  - f. Active liver disease;
  - g. Pregnancy or lactation period;

**\*Severe heart failure:** New York Heart Association (NYHA) Classification III and IV

I Cardiac disease, but no symptoms and no limitation in ordinary physical activity, e.g. no shortness of breath when walking, climbing stairs etc.

II (mild heart failure) Mild symptoms (mild shortness of breath and/or angina) and slight limitation during ordinary activity.

III (moderate heart failure) Marked limitation in activity due to symptoms, even during less-than-ordinary activity, e.g. walking short distances (20–100 m). Comfortable only at rest.

IV (Severe heart failure) Severe limitations. Experiences symptoms even while at rest. Mostly bedbound patients.

7. Pre-existing disability with mRS score  $> 2$ .
8. Intra- arterial or intravenous thrombolysis or endovascular therapy after onset.
9. Defibrinogen therapy (e.g. defibrase and lumbrokinase), anticoagulation therapy (e.g. argatroban) , or antiplatelet therapy (e.g. ticagrelor, tirofiban) except for clopidogrel and aspirin after onset.
10. Creatine kinase  $> 5$  times the upper limit of normal value of onset.
11. Drug use related to statin metabolism within 14 days before randomization (e.g. immune-suppressive drugs, antifungal agents, fibrates).
12. Severe hepatic insufficiency (ALT or AST  $> 2$  times the upper limit of normal value) or renal insufficiency (creatinine  $> 1.5$  times the upper limit of normal value or glomerular filtration rate  $< 40$  ml/min/1.73 m^2).

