### 16.3.1 Statistical analysis of data sets

**Full Analysis Set (FAS):** The full analysis set is the main efficacy evaluation population of this study, and all valid variables will be analyzed by FAS. According to the basic principle of intention-to-treat (ITT) analysis, all subjects randomized into groups and those with more than one medication record and efficacy evaluation will be included in the full analysis set. When choosing FAS to analyze, the estimate of the missing value, the last observation carried forward (LOCF) estimation method can be used.

**Per Protocol Set (PPS):** Includes all subjects who complete the protocol or have no serious breaches of the trial. The exact definition of a serious violation of the program will be finalized at the time of data review and may generally include the following situations (but not limited to these cases): failing to meet the main inclusion criteria, serious disturbance of drug efficacy after treatment, poor compliance, exceeding the time window of following-up and so on. PPS is the secondary analysis of the effectiveness of the crowd, but if the results are inconsistent with the whole analysis set, detailed analysis of the

inconsistent results are needed.

**Safety Data Set (SS):** A safety data set is defined as a subject that receives drug treatment at least once. In the entire safety analysis, patients with incorrect treatment (for example, randomized to the standard antiplatelet combining delayed intensive statin therapy groups were given enhanced antiplatelet therapy) would be assigned to the actual treatment group.

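### Laboratory harms are mainly analysed as normal-to-abnormal cases, but the muscle-toxicity outcome has no baseline condition and patients with CK up to 5 × ULN may enter

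*Supplement*

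**What the plan says.** This concerns the latest protocol (version 4.0). No separate SAP is shown.

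- **Outcome.** Section 2.3 asks, for each factor and for the combination, for an evaluation in "patients attributed to intracranial or extracranial atherosclerosis on the incidence of" a list of harms. One of them is "Muscle toxicity: Creatine kinase (CK) > 10 times the upper limit of normal value, or the presence of muscle pain, myopathy, or rhabdomyolysis". Section 4.4 repeats the muscle definition ("times the upper limit of normal value, or the presence of muscle pain, myopathy, or rhabdomyolysis") and sets hepatotoxicity at ALT or AST above 3 × ULN. Neither section makes the outcome depend on the baseline value.
- **Analysis.** Section 16.3.2.2, part 3, gives Kaplan-Meier and Cox methods for moderate to severe bleeding, intracranial hemorrhage and overall mortality. The remaining adverse events and abnormal laboratory results get a different rule: "the cases which was normal before the treatment and abnormal after the treatment would be mainly analyzed and listed". The Summary states the same rule, "in addition to the comparison of differences before and after treatment".
- **Data and population.** Section 16.3.2.2 also says: "The safety evaluation data includes adverse reactions observed during the trial and changes in laboratory data before and after treatment". Section 16.3.1 says: "A safety data set is defined as a subject that receives drug treatment at least once".
- **Eligibility.** Exclusion 10 in section 5.2 removes patients whose CK is more than 5 "times the upper limit of normal value of onset". Exclusion 12 removes ALT or AST above 2 × ULN.

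**The concern.** The outcome is unconditional, but the stated analysis rule depends on baseline. A patient who enters with raised CK cannot be normal before treatment, so a later rise past 10 × ULN is an outcome event that the rule does not clearly count. Muscle toxicity is a named secondary safety outcome, and the timing and dose of atorvastatin is one of the two randomized factors. The main tabulation of CK cases could therefore fall short of the incidence that sections 2.3 and 4.4 promise, and a reader could not tell which of the two was reported.

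**Working it through.** The plan gives no figure to reproduce. The check sets thresholds and timings side by side.

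**1. Which rule reaches CK and transaminases?** The only safety outcomes given a model by name are bleeding, intracranial hemorrhage and mortality. The next sentence covers the remaining adverse events and laboratory abnormalities. It is the only sentence in section 16 that can govern the laboratory part of the two toxicity outcomes.

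**2. CK.**
- Entry limit: 5 × ULN (exclusion 10). Outcome threshold: above 10 × ULN (section 4.4).
- The protocol gives no other threshold for an abnormal CK and scales CK to the upper limit of normal. The affected group is therefore baseline CK above 1 and up to 5 × ULN.
- Rise that must be exceeded to meet the outcome = 10 ÷ baseline multiple:
  - from 5 × ULN: 10/5 = 2-fold
  - from 3 × ULN: 10/3 = 3.3-fold
  - from 1 × ULN (lower edge of the group): 10/1 = 10-fold
- Example: entry at 3 × ULN, later 15 × ULN, no muscle symptoms. The section 4.4 outcome is met; the normal-before condition is not.
- Muscle pain, myopathy or rhabdomyolysis meets section 4.4 at any CK value. Only asymptomatic rises are in question.

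**3. Transaminases.**
- Entry limit: 2 × ULN. Outcome threshold: above 3 × ULN.
- Section 7.5.1 (item 5) and Appendix 7 treat transaminases as abnormal only above twice normal. On that reading, every eligible patient (at most 2 × ULN) is normal before, and every outcome case (above 3 × ULN) is abnormal after. No affected group remains.
- If normal instead means at most 1 × ULN, the affected group is above 1 and up to 2 × ULN, and the rise to be exceeded runs from 3/2 = 1.5-fold to 3/1 = 3-fold.

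**4. Where the baseline CK comes from.**
- The screening tests listed in section 10.1 and in note 2 of section 10.9 are blood routine, transaminases, renal function and clotting. CK is not listed.
- Section 10.2 puts the first dose within 1 hour of randomization. It schedules the first panel that names CK within 24 hours after randomization, at latest 72 hours.
- Exclusion 10 nevertheless requires a CK value to decide eligibility. The Day 7 waiver in section 10.3, for tests done within 24 hours of screening or randomization, also allows for CK at screening. A pre-randomization CK is thus implied but not written into the schedule.

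**The case against.** The strongest case against the point has four parts.

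- **The sentence may be a listing rule for residual events only.** Section 4.4 lists the two toxicity outcomes apart from other AEs and SAEs, and section 2.3 already asks for their incidence. This reading is possible. The two outcomes would then have no stated comparison. Section 16.3 leaves such detail to a later SAP, so that alone would not be a finding. But the sentence covers laboratory abnormalities and only three other outcomes are set apart by name, so the reading that includes CK is at least as natural. On that reading a stated rule conflicts with a stated outcome. The same wording change settles both readings.
- **The rule is not exclusive.** It says mainly, laboratory changes before and after treatment are also evaluated, and every treated patient is in the safety set. This stands: such cases are not certainly lost. Still, a comparison of values before and after treatment is not the incidence of CK above 10 × ULN by arm.
- **Normal CK could mean anything up to 5 × ULN, by analogy with transaminases.** This fails. For transaminases the protocol itself labels values above twice normal as abnormal. For CK it gives no such label, and an exclusion limit is not a definition of normal.
- **A pre-dose CK is already needed for exclusion 10.** This stands. A reader might infer from section 10.2 that eligibility, or the normal-before label, rests on a CK drawn after 1 to 3 daily doses (80 to 3 × 80 = 240 mg in the immediate arm, 0 mg in the delayed arm). The documents do not support that, because exclusion 10 refers to CK at onset and must be checked before randomization. What remains is a schedule that does not name a test the criteria require.

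**Conclusion.** The point holds as a minor mismatch between a stated rule and a stated outcome. An asymptomatic CK rise above 10 × ULN from an entry value above 1 and up to 5 × ULN meets section 4.4 but falls outside the normal-to-abnormal rule as worded. Its size is unknown, because the documents do not give the share of patients entering with raised CK. The conclusion assumes that the rule is meant to cover the laboratory part of the named outcomes and that normal CK means no higher than the upper limit of normal.

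Two stronger readings should be resisted. One is that patients with abnormal baseline tests are dropped from the safety analysis; the definition of the safety set and the before/after evaluation contradict this. The other is that the statin comparison is biased; entry CK is limited alike in all arms of a randomized, blinded trial, and nothing in the documents shows a difference between arms.

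**What to change.** - In section 16.3.2.2 and the Summary, state that the section 4.4 hepatotoxicity and muscle-toxicity outcomes are compared between arms in the whole safety set, regardless of baseline.
- Keep the normal-to-abnormal listing as supplementary, with a shift table by baseline category (CK: normal, above 1 to 5 × ULN; ALT and AST: normal, above 1 to 2 × ULN).
- Define baseline as the last value before the first dose.
- For consistency with exclusion 10, name CK among the screening tests in section 10.1 and in note 2 of section 10.9.

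The cost is a few lines of wording and one table; the CK test is already implied by exclusion 10. The downside is slightly more analysis and possibly a slightly higher reported toxicity rate.

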### 3. Study Design

#### 3.1 Study design

- A Randomized, double-blind, placebo-controlled, multicenter, 2×2 factorial trial
- The trial is intended to enroll 6100 subjects and complete follow-up of all subjects within 5 years.
- Centralized, unified and randomized grouping.
- Subjects will be randomly assigned to the following four groups:
  - A:** Intensive antiplatelet therapy +immediate intensive statin therapy (atorvastatin 80mg/d)
  - B:** Intensive antiplatelet therapy +delayed intensive statin therapy (atorvastatin 40mg/d)
  - C:** Standard antiplatelet therapy +immediate intensive statin therapy (atorvastatin 80mg/d)
  - D:** Standard antiplatelet therapy +delayed intensive statin therapy (atorvastatin 40mg/d)

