## **7. Study Implementation**

### **7.1 Randomization procedures**

Random number lists will be generated by the Statistics and Data Center at the China National Clinical Research Center for Neurological Diseases (Beijing, China). Regimens for patients will be packed according to the random code lists. Patients will be assigned to four groups with the approximate ratio of 1:1:1:1, and receive: A intensive antiplatelet therapy+ immediate intensive statin therapy (atorvastatin 80mg/d), B intensive antiplatelet therapy+ delayed intensive statin therapy (atorvastatin 40mg/d), C standard antiplatelet therapy+ immediate intensive statin therapy (atorvastatin 80mg/d), or D standard antiplatelet therapy+ delayed intensive statin therapy (atorvastatin 40mg/d) respectively. Randomization will be centralized. We applied randomized block design to generate random number to ensure the ratio between the four groups will be approximately 1:1:1:1. If a center runs out of its random code lists, a new block will be placed to the center for new random numbers. Each patient eligible to the INSPIRES trial will be assigned a random number in order strictly and the corresponding study drug box.

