### 16.1 Estimate Sample Size

The minimal sample size for the trial is determined by the necessity that a clinically meaningful difference in effectiveness between treatment and control groups has to be detected. Based on previous studies, the risk of new stroke during 90 days is presumed to be 11.5% in the group with standard antiplatelet therapy (with half delayed intensive statin therapy and half early high-intensity statin therapy) and 11.5% in the delayed intensive statin therapy group (with half standard antiplatelet therapy and half dual antiplatelet therapy) and 13% in the group with standard antiplatelet therapy plus delayed intensive statin therapy, intensive antiplatelet therapy and immediate intensive statin therapy can reduce this risk by 22%, and the effects of intensive antiplatelet and lipid lowering therapy will be similar and additive. With a sample size of 6100 subjects, a two-sided  $\alpha$  of 0.05 and 5% loss to follow up, we will have 97% power to detect that the risk is decreased by 35% in the group with dual antiplatelet therapy plus immediate intensive statin therapy compared to standard antiplatelet therapy plus delayed intensive therapy, and 80% power to detect that the risk is reduced by 20% by intensive antiplatelet therapy compared to standard antiplatelet therapy, and immediate intensive statin compared to delayed intensive statin therapy, respectively.

**Table1 For different risk rates (12% to 14%) of the results in the control group, the sample size required for observing intensive antiplatelet combining intensive statin therapy**

| Power | A single set of sample size (no expulsion) | A single set of sample size (5% expulsion rate) | Four groups of sample size | The stroke recurrence rate in treatment group | The stroke recurrence rate in control group | Relative risk |
|-------|--------------------------------------------|-------------------------------------------------|----------------------------|-----------------------------------------------|---------------------------------------------|---------------|
| 0.966 | 1448                                       | 1525                                            | 6100                       | 0.078                                         | 0.120                                       | 0.65          |

|       |      |      |      |       |       |      |
|-------|------|------|------|-------|-------|------|
| 0.975 | 1448 | 1525 | 6100 | 0.085 | 0.130 | 0.65 |

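### For hepatotoxicity and muscle toxicity the protocol asks for a comparison between regimens, but the only comparison it names is before versus after treatment

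*Supplement*

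**What the plan says.** Section 2.3 lists hepatotoxicity (ALT or AST above 3 times the upper limit of normal, ULN) and muscle toxicity (CK above 10 times ULN, or muscle pain, myopathy or rhabdomyolysis) under each of three contrasts: antiplatelet, statin, and combined versus control. The statin one reads "To evaluate safety of immediate intensive statin therapy (atorvastatin 80mg/d) versus delayed intensive statin therapy (atorvastatin 40mg/d) for 90 days". Section 4.4 makes both outcomes secondary safety outcomes. Section 1.3.2 gives a higher rate of intolerance to intensive statins in Chinese patients as one reason to study the two doses.

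Section 16.3.2.2, item 3, assigns Kaplan-Meier curves and Cox hazard ratios to moderate-to-severe bleeding, intracranial hemorrhage and overall mortality. For other adverse events and laboratory abnormalities, the cases normal before and abnormal after treatment "would be mainly analyzed and listed, in order to the comparison of differences before and after treatment". Summary 3.3 says the same cases are analyzed and listed "in addition to the comparison of differences before and after treatment". The chi-square and Fisher wording in section 16.3.2.1 concerns baseline indicators only.

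Section 16.3.1 places wrongly treated patients in the safety set under the treatment they received. Section 16.3 calls itself an overview and defers to a SAP, to be finished before database lock, that is not among the documents.

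**The concern.** A before-after comparison asks whether patients changed since baseline. Section 2.3 asks whether one regimen is more toxic than another. These are different estimands, and only the second uses the randomization.

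The gap matters most for the statin factor. Both statin groups take active atorvastatin from Day 4, so some new liver or muscle abnormalities can be expected in both even if the regimens are equally toxic. Eligibility adds to this. Exclusion 12 removes "Severe hepatic insufficiency (ALT or AST $> 2$ times the upper limit of normal value", and exclusion 10 removes CK above 5 times ULN. Both limits lie below the outcome thresholds, so by the criteria nearly every later laboratory case is a change in one direction. A before-after result could then look positive in both groups and say nothing about the dose question that section 1.3.2 raises.

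**Working it through.** **1. Which method goes with which outcome**

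| Outcome | Contrast asked for (section 2.3) | Method named (section 16.3.2.2, Summary 3.3) |
|---|---|---|
| Bleeding, intracranial hemorrhage, death | Between regimens | Kaplan-Meier, Cox hazard ratio |
| Hepatotoxicity, muscle toxicity | Between regimens | None by name; if they fall under other adverse events and laboratory abnormalities, listing and before-after comparison |

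The mismatch shows here without any arithmetic. The remaining steps ask how much it could matter.

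**2. Inputs**

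- Total size: "The trial is intended to enroll 6100 subjects" (section 3.1).
- Allocation: "Patients will be assigned to four groups with the approximate ratio of 1:1:1:1" (section 7.1), so 6100 / 2 = 3050 per level of each factor.
- Losses: "5% loss to follow up" (section 16.1). Table 2 there gives 2896 evaluable per level.
- Alpha: 0.05; "A two-sided test will be used for all statistics" (Summary 3.2).
- Assumed, because the documents give neither: an exact McNemar test, and event rates of 0.1% to 1.0%.

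**3. Check of the per-level size**

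The plan's Table 2 has rates 0.0930 and 0.1157 with n = 2896. The difference is 0.0227 and the pooled rate 0.10435. SE under the null = sqrt(2 × 0.10435 × 0.89565 / 2896) = 0.00803, and SE under the alternative is also 0.00803. Power = Φ(0.0227 / 0.00803 − 1.96) = Φ(0.87) = 0.807, the stated value.

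**4. A paired test with no cases at baseline**

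All discordant pairs point the same way, so with k new cases p = 2 × 0.5^k. For k = 5, p = 0.0625; for k = 6, p = 0.031. The test rejects from 6 cases on. The rejection rate within one level is P(X ≥ 6) with X binomial (2896, rate), whatever happens in the other level.

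| Assumed rate | Expected cases per level | Before-after rejects, one level |
|---|---|---|
| 0.1% | 2.9 | 7% |
| 0.2% | 5.8 | 52% |
| 0.3% | 8.7 | 86% |
| 0.5% | 14.5 | 99.6% |
| 1.0% | 29.0 | about 100% |

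Both levels reject together, with identical arms, in 27% of simulated trials at 0.2% and 99% at 0.5%.

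**5. A comparison between levels**

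A two-proportion test (20,000 simulated trials, 2896 per level) rejects in 4% to 5% of trials when the arms are identical, at every rate from 0.1% to 2%. For a true doubling it rejects in 60% (0.5% to 1.0%) and 89% (1.0% to 2.0%).

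**6. Two hypothetical results**

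- *15 versus 15 cases.* Paired p = 2 × 0.5^15 = 0.00006 in each level. Risk difference 0; SE = sqrt(2 × 0.00518 × 0.99482 / 2896) = 0.00189; 95% CI −0.37 to +0.37 percentage points.
- *15 versus 29 cases.* Paired p = 0.00006 and below 0.00001. Risk difference 14 / 2896 = 0.48 percentage points; SE = sqrt((0.00518 × 0.99482 + 0.01001 × 0.98999) / 2896) = 0.00228; 95% CI 0.04 to 0.93.

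The paired verdict is the same in both; only the risk difference separates them.

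**The case against.** The strongest reply is that the plan contains no such test. The sentence is garbled and its two forms differ. It speaks of cases being analyzed and listed, and names no paired test, P value or null hypothesis. Section 16.3.2.2 also uses before and after treatment to describe the laboratory data themselves, so the phrase may mean the variable and not the contrast. This stands: the rejection rates above describe one possible implementation.

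Second, the SAP may supply the between-arm method, and its absence from an overview is no fault. That stands for silence. Here, however, the protocol names a comparison in two places, and it does not match its own objective.

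Third, section 4.4 lists the two toxicities apart from other adverse events, so the sentence may not govern them. That is possible. The laboratory components are nevertheless laboratory abnormalities, and no other safety sentence covers them.

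A reader might infer that the before-after comparison rejects almost regardless of any arm difference, or that it would hide a real excess. The documents support neither:

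- Under the assumed test, rejection falls to 52% at 0.2% and 7% at 0.1%.
- New cases tabulated by actual treatment would still show an excess in one arm.
- The zero baseline is not secure for muscle toxicity. Muscle pain at entry is no exclusion, and CK is not among the screening tests in section 10.1; it first appears in the fasting panel of section 10.2, after randomization.

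**Conclusion.** The point holds as a mismatch between objective and named analysis. For two secondary safety outcomes with three stated contrasts, the only comparison that the protocol names measures change since baseline, and it names no between-regimen estimate. This conclusion needs no assumption about tests or rates, though it takes the sentence on laboratory abnormalities to cover these outcomes.

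The size of the consequence is conditional. If a formal exact McNemar test were used and no patient met the definition at baseline, it would usually reject with identical arms at event rates of about 0.5% or more per factor level, and would not do so at 0.1%. Both the test and the rates are assumptions. The change is worth making because the statin dose question rests partly on tolerability.

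**What to change.** Reword item 3 of section 16.3.2.2 and Summary 3.3 so that they agree, and carry the wording into the SAP:

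- Compare the proportion with hepatotoxicity and the proportion with muscle toxicity, as defined in section 4.4, between the two levels of each factor and for combined versus control.
- Use the safety set, grouped by actual treatment as section 16.3.1 already provides.
- Report a risk difference or ratio with a 95% confidence interval, exact or from logistic regression, stratified by the other factor for the two marginal contrasts.
- Keep before-after shifts and case listings as description by arm, without P values.

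The cost is a change of wording and one table per contrast. No new data are needed: the section 10.9 schedule already includes liver enzymes and CK at Day 7 (waived if done close to screening or randomization) and Day 90, and adverse events at each follow-up visit.
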